### Participants and randomization

Potentially eligible participants will be identified and recruited both at CHOP and COH through existing databases and physician referrals. Study staff will pre-screen potential participants by reviewing the medical charts and exclude those who do not meet inclusion/exclusion criteria {15}. Individuals who meet the eligibility criteria (Table 2) will be invited to enroll. All participants will be enrolled when they provide written consent to the principal investigator(s) either virtually or in-person and all the initial eligibility requirements are met {26a}. Once eligibility is confirmed via in-person screening procedures, participants will be randomized into one of four arms, with randomization stratified by age (≥ 18y or < 18y) and site (CHOP or COH) by a designated study member using REDCAP randomization scheme (Fig. 2) {16b} {16c}. Balance between arms will be maintained through randomly permuted blocks of size four or eight {16a}. The research team, outcomes assessors, care providers, and participants will be blinded with respect to whether participants are receiving NR vs. placebo. NR and placebo are dispensed in identical capsules to avoid un-blinding. The outcomes assessor (but not the study team, care providers, or participants) will be blinded with respect to whether individuals are receiving the in-home exercise intervention vs. no exercise intervention {17a}. The Investigator will be unblinded only if an AE occurs that is determined to be serious, and treatment for the adverse event (AE) depends on knowing the group assignment. Participants/families will be unblinded at the completion of the entire study {17b}. The current study has been approved by the Institutional Review Board of Children’s Hospital of Philadelphia (approval number: IRB #17,320) and has been pre-registered at www.clinicaltrials.gov (NCT05194397). The Standard Protocol Items: Recommendations for Interventional Trials (SPIRIT) guideline was used to generate the report [27].

**Table 2 Tab2:** Inclusion and Exclusion Criteria {10}

Inclusion Criteria	Exclusion Criteria

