#### Dynamometry (hand grip, lower extremities)

Trained personnel will perform testing at CHOP and COH. A dynamometer (Takei Scientific Instruments Co., Ltd., Japan) will be used to measure instantaneous hand grip strength because in epidemiological studies this index of muscle strength has been shown to be associated with morbidity and mortality [28]. Three trials will be performed using each hand, and the maximum value will be recorded (N). The Biodex Dynamometer (Biodex Corp., Shirley, NY) will be used to measure muscular strength in the ankle and knee. Participant will perform isometric strength tests, with three repetitions performed at each position. A 5 s rest is given between repetitions. At each position, peak torque (N) will be recorded. References will be used to generate age- and sex-specific Z-scores [29].

*CrCEST MRI* is a non-invasive way to test skeletal muscle OXPHOS capacity [30]. With CrCEST, creatine content can be simultaneously measured in every muscle of the leg [31, 32]. CrCEST is used to determine the exponential time constant for the decline in creatine post-exercise (τCr) in each muscle of the calf (lateral gastrocnemius, medial gastrocnemius, and soleus) after an in-magnet standardized exercise on an MR-compatible. Prolonged τCr is suggestive of decreased OXPHOS capacity. In a “proof-of-principle” study using CrCEST at a 7 T MRI field strength [33], our team found that individuals with genetic diseases affecting mitochondria had significantly prolonged post-exercise τCr in the medial gastrocnemius muscle, indicating decreased OXPHOS capacity. Using CrCEST, we also found that habitual exercise duration is positively associated with muscle OXPHOS in individuals with genetic mitochondrial disorders [33]. In a separate study using CrCEST at 3 T, we found that decreased physical activity in individuals with Friedreich’s Ataxia, a neurological disorder, accounted for some of the difference in τCr in lateral gastrocnemius between individuals with Friedreich’s Ataxia and healthy controls [34]. We will use the same 3 T CrCEST to examine the effects of mitochondria-targeted interventions in the present study.

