### Statistical considerations

Linear mixed-effects modeling will be used to evaluate effect of interventions over time on the primary and key secondary outcomes. The models incorporate subject-specific random effects to account for within-subject correlation due to repeated measures. Group averages, as well as subject-specific intercepts and slopes, will be estimated to capture potential variations in the baseline values and slopes among individuals. Linear mixed-effects models accommodate missing data due to dropout, such that all randomized participants can be included. We will compare participants who complete the study with those who do not and identify potential factors that are associated with dropout {20c}. In the mixed-effects models, we will adjust for time-invariant covariates (age at randomization, sex) and time-varying covariates (muscle strength, lean mass, muscle OXPHOS capacity, VO2max). By including these indices of “muscle quality” as covariates in the models, we will be able to assess whether intervention effects are explained by these effects. To assess other potential factors influencing outcomes, we will also analyze the incremental effect of adding each of the other measured covariates (final dose of NR achieved, final training intensity achieved) to the models.

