The primary outcome for our study is the change in muscle strength (quadriceps extension, Z-score) from baseline to 16 weeks. We expect exercise and NR to each produce an increase (relative to control/placebo) with respect to the primary outcome of muscle strength from baseline to week 16. We posit that the effects of exercise and NR in combination will be additive and possibly even synergistic. Despite our strategies to track and optimize adherence, it is possible that the change in Z-score will vary across participants in response to one or both interventions. We will fit a linear model with the outcome of change in Z-score of muscle strength and covariates of treatment arm and baseline Z-score. Using a modification of previous strategies for the analysis of factorial designs, the family-wise Type I error rate is maintained at < 5% by using a two-stage approach: a Holm-Bonferroni correction is applied in Stage 1, and a single contrast is pre-specified in Stage 2 [43]. In Stage 1, we will test if the mean Z-score in each of the 3 active treatment arms differs from control (no-exercise + placebo). In Stage 2, if the exercise + NR arm differs from the control arm, we will then compare exercise + NR to exercise alone, to determine whether NR increases mean Z-score beyond the effect of exercise alone; 95% confidence intervals will be determined for each effect of interest.

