In addition, we expect exercise and NR to each produce an increase (relative to control/placebo) with respect to the secondary outcome of VO_2_max. We expect that the effects of exercise and NR in combination will be additive, and possibly even synergistic. The effect of sex will also be assessed. The analysis for VO_2_max Z-score (Aim 2) will be the same as for Aim 1, since both outcomes are expressed as a Z-score. We will fit a linear model with the outcome of change in Z-score of VO_2_max and covariates of treatment arm and baseline Z-score for VO_2_max {8} {20a}.

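### Randomisation is stratified by age group and site, but the linear models written for strength and VO2max include neither and site is in no model, so inference will be conservative if the strata are prognostic.

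*Protocol article*

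**What the plan says.** Under Participants and randomization, the protocol article describes "randomization stratified by age (≥ 18y or < 18y) and site (CHOP or COH"), which makes four strata. On blocking it adds: "Balance between arms will be maintained through randomly permuted blocks of size four or eight".

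Statistical considerations describes two kinds of model.

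- **Linear model of change.** For the primary outcome: "We will fit a linear model with the outcome of change in Z-score of muscle strength and covariates of treatment arm and baseline Z-score". The model given for VO2max has the same two terms, with its own baseline value. The primary analysis is also to be repeated for each secondary outcome, so the same covariate list carries over. Neither age group nor site is in it.
- **Mixed-effects model.** The section opens with: "Linear mixed-effects modeling will be used to evaluate effect of interventions over time on the primary and key secondary outcomes". For these models, "we will adjust for time-invariant covariates (age at randomization, sex"), together with time-varying muscle and fitness measures. Age is therefore present here, but site is not.

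The exploratory models later in the section list age at randomisation, sex and clinical characteristics. Site is not named there either. The section does not say which of the two kinds of model is the primary analysis.

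On the outcome scale, the dynamometry section says: "References will be used to generate age- and sex-specific Z-scores".

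**The concern.** Stratified blocking removes part of the between-stratum variation from the arm comparisons. The analysis gets credit for this only if the model contains the strata. If it does not, and the strata are prognostic, their variance stays in the residual. The estimated standard error then describes a less precise design than the one that was run: intervals are too wide and tests reject less often than their nominal level.

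This matters most in a small trial with a gated test sequence. The plan expects 16 participants per arm with complete data. The testing rule is that "a Holm-Bonferroni correction is applied in Stage 1, and a single contrast is pre-specified in Stage 2", and the comparison of exercise + NR with exercise alone is reached only if exercise + NR first differs from control. Conservatism in Stage 1 therefore also makes Stage 2 harder to reach. In addition, drop-out can unbalance the sites across arms, and a model without site cannot correct for that.

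**Working it through.** **Inputs from the protocol article.** 80 randomised to four arms; 20% attrition; 64 with complete data, 16 per arm; blocks of four or eight within four strata; 80% power for a 0.73 Z-score difference between exercise + NR and exercise alone.

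**Assumptions.** A two-sided 5% test for that contrast (sidedness is not stated). R2 is the share of residual variance, after baseline Z-score, explained by age group and site. The documents give no value, so a range of 0 to 0.20 is used.

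**Step 1: the plan's own figures.** 64 / (1 − 0.20) = 80 reproduces the sample size. The 80% power cannot be reproduced forward, because no SD of the change in strength Z-score is stated. (The only SD given, 1.4, is for muscle area.) Solving backwards with 16 per arm, 80% power at 0.73 needs a residual SD of 0.737 (normal approximation) or 0.725 (t distribution, 59 df). The 59 is 64 minus 5 parameters: intercept, three arm terms and baseline.

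**Step 2: analytic effect of adding the strata.** With exact balance, the unadjusted model overstates the standard error by 1/√(1 − R2):

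- R2 0.05: 1/√0.95 = 1.026
- R2 0.10: 1/√0.90 = 1.054
- R2 0.20: 1/√0.80 = 1.118

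For the adjusted model, SE = 0.725 × √(1 − R2) × √(2/16), and the noncentrality is 0.73/SE with 57 df. At R2 = 0, SE = 0.256, noncentrality 2.85, power 80.0%. At R2 = 0.20, SE = 0.229, noncentrality 3.18, power 87.9%. At 0.05 and 0.10 power is 81.9% and 83.9%.

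The true size of the unadjusted 5% test under exact balance is the two-sided tail beyond 2.001/√(1 − R2) on 59 df. This is 4.5% at R2 0.05, 3.9% at 0.10 and 2.9% at 0.20. For the strictest Holm step (0.05/3 = 0.0167, critical value 2.464), the same calculation gives 0.012 at R2 0.10 and 0.008 at 0.20.

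**Step 3: simulation with the planned attrition.** Drop-out loosens the balance, so 12,000 trials per setting were simulated. Each randomised 80 people within four strata in blocks of four or eight and analysed a random 64. Further assumptions: total residual SD 0.713 (the value giving 80% power on 30 df), 30% in one age group, equal sites, and R2 split equally between age group and site. The contrast is exercise + NR against exercise alone.

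| Assumed R2 | Mean model SE, no strata (true SD of estimate) | Size, no strata | Power, no strata | Power, with strata |
|---|---|---|---|---|
| 0 | 0.254–0.255 (0.254–0.258) | 5.2% | 79.7% | 79.0% |
| 0.05 | 0.255 (0.249–0.251) | 4.6% | 80.2% | 81.4% |
| 0.10 | 0.255 (0.247–0.248) | 4.5% | 81.0% | 83.9% |
| 0.20 | 0.256 (0.236–0.239) | 3.4% | 81.6% | 87.3% |

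With the strata in the model, size was 5.0 to 5.2% throughout. The Monte Carlo standard error is about √(0.05 × 0.95/12,000) = 0.2 points for size and √(0.8 × 0.2/12,000) = 0.4 points for power, so 5.2% at R2 = 0 is compatible with 5%. The loss of size is milder than under exact balance (4.5% against 3.9% at R2 0.10).

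**The case against.** The strongest objection is that R2 may be close to zero.

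- **Age.** Strength is scored against age- and sex-specific references, which should remove much of any age effect. The outcome is also a within-person change with baseline in the model.
- **Site.** The article names one make of each dynamometer without a site difference, and the same gas-exchange system for both sites. Exercise training is overseen remotely for both sites from a third institution. A constant measurement offset between sites mostly cancels from a change score: after baseline adjustment only (1 − slope) × offset is left. With two equal sites, residual SD 0.725 and assumed follow-up-on-baseline slopes of 0.7 to 0.9, a 0.5 Z offset explains 0.1 to 1.1% of residual variance and a 1.0 Z offset 0.5 to 4.1%. For example, at slope 0.7 and offset 1.0: (0.3/2)² = 0.0225, and 0.0225/(0.5256 + 0.0225) = 4.1%.

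This stands as an argument about size. It does not cover site differences in response, adherence or case mix, for which the documents give no figure.

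A second objection is that one stratification factor is already handled, because the mixed-effects model for the same outcomes adjusts for age at randomisation. That is correct, so it would be wrong to say that nothing in the plan adjusts for age. Site is still absent, and the linear model to which the two-stage testing is attached has neither factor.

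A third is that a condensed article leaves such detail to the full protocol or SAP. That would answer a silence. Here the covariate list is written out, and it departs from the randomisation scheme.

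**Conclusion.** The point holds as a mismatch between design and stated analysis, with a conditional consequence. The linear models for strength and VO2max leave out both stratification factors, and site is in no model described. If age group or site predicts change in Z-score after baseline, standard errors will be too large and tests conservative.

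A reader might infer more than this, in two ways. One is that the standard errors are certainly too large and power is being lost. The documents give no R2, and their use of age- and sex-specific change scores and common equipment suggests it may be small. At R2 of 0.05 adjustment gains about 1 power point, at 0.10 about 3 and at 0.20 about 6; at 0 it costs slightly. The other is that the stated 80% power is wrong or that false positives increase. Neither follows: simulated power of the unadjusted model stays between 79.7 and 81.6% over this range, and its size does not rise above nominal beyond simulation error.

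The omission is certain from the text. The size of its effect is not, and rests on the assumed R2, a back-solved residual SD and drop-out at random.

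**What to change.** Add site and age stratum (under 18, or 18 and over) as fixed effects to the linear model for change in strength Z-score, to the corresponding VO2max model, and to the repeats of the primary analysis for the other secondary outcomes. Add site to the mixed-effects model, which already contains age at randomisation. State in the same place which of the two models is primary, so that it is clear where the covariate list applies. Fix this before any unblinded data are seen.

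The cost is a sentence or two of wording and 2 of 59 residual degrees of freedom (57 remain; 56 if the four strata are coded with three indicators). If the strata turn out not to be prognostic, the simulated loss is 0.7 power points (79.7 to 79.0%). Sample size, randomisation and data collection do not change.

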### Sample size and power

With the proposed design, we have > 80% power to detect four scenarios of treatment-related changes in mean Z-score of 0.93–1.66 accounting for multiple testing with a family-wise Type I error rate < 5%. Notably, we have 80% power to detect a difference between exercise and exercise + NR (Scenario 1) of 0.73 Z-score. We have demonstrated that increases in muscle group specific strength of up to 100% (absolute amount) over 24 weeks are plausible, depending on the degree of initial deficits and muscle group tested [45]. In a 12-week pilot study, a mean increase of quadriceps strength of 14% was observed [46]. In a previous meta-analysis in adults, effect sizes of 0.53–0.79 were reported with supervised aerobic exercise [47, 48]. We anticipate that increases in the present study may be even larger for several reasons. First, these relatively young participants will have substantial muscle deficits, thus there is a clear opportunity to demonstrate benefit. Our preliminary data indicate muscle deficits in HCT survivors, with low Z-scores for muscle area (mean -0.9, SD 1.4). Also, we have chosen to intervene at the soonest potential opportunity post-HCT, thus we expect muscle deficits will be less established and participants will be more responsive to the interventions. Our team has considerable experience in supervising, individualizing, and adjusting the exercise regimen to achieve maximum benefit. Also, we will randomize 80 participants to achieve 64 (*n* = 16 in each of 4 arms) with complete data (i.e., conservatively allowing 20% attrition) {14}.

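### The two-stage testing rule, as written, does not hold the two-sided family-wise error below 5%: if exercise works and NR is inert, it can rise to 9.75%

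*Protocol article*

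**What the plan says.** Under Statistical considerations, the primary outcome (change in knee-extension strength Z-score) is analysed in a linear model with "covariates of treatment arm and baseline Z-score". The article states that "the family-wise Type I error rate is maintained at < 5% by using a two-stage approach", and describes the rule: "a Holm-Bonferroni correction is applied in Stage 1, and a single contrast is pre-specified in Stage 2".

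- Stage 1: "we will test if the mean Z-score in each of the 3 active treatment arms differs from control".
- Stage 2: "if the exercise + NR arm differs from the control arm, we will then compare exercise + NR to exercise alone".

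No level is given for Stage 2, no alpha is reserved for it, and no reduced Stage 1 level is mentioned. The same paragraph adds that "95% confidence intervals will be determined for each effect of interest". Sample size and power repeats the error-rate claim, describing the power as "accounting for multiple testing with a family-wise Type I error rate < 5" per cent. The same analysis is carried over to the secondary outcomes, including VO2max.

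**The concern.** There are four hypotheses, but Holm covers only three. The fourth opens once exercise + NR versus control is rejected. That gate protects Stage 2 when the combination is no better than control. It does not protect when exercise alone produces the rejection.

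Suppose exercise works and NR does nothing. The two false nulls (exercise versus control, exercise + NR versus control) tend to be rejected. Two things follow:

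- Holm moves on to NR versus control and tests it at the full 5%.
- The gate opens, and exercise + NR versus exercise is tested as a single contrast with no stated correction.

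Both remaining hypotheses are true nulls, and both concern NR. At stake is a stated property of the primary analysis, on which the power statement also relies. The article expects exercise to work, and Stage 2 asks whether NR adds anything to it, so this null configuration is not remote.

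**Working it through.** **Inputs.** From Sample size and power: 80 randomised, 20% attrition, 64 completers, 16 per arm; 80% power for a Stage 2 difference of 0.73 Z; powered effects 0.93 to 1.66 Z. From Statistical considerations: Holm at 5% over three tests, and the Stage 2 gate. Assumed: two-sided tests (the text asks whether arms differ) and Stage 2 at 5%.

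**The plan's own figures.** 64 / (1 − 0.20) = 80, as stated. The SD of the change is not given, so the 80% power can only be solved backwards. By the normal formula, SD = 0.73 / [(1.960 + 0.842) × √(2/16)] = 0.737. With the t distribution on 64 − 4 − 1 = 59 degrees of freedom it is 0.725. This back-solution itself assumes Stage 2 at 5%; at 2.5% the SD would be 0.655, and at 5%/3 it would be 0.623. The only SD printed is 1.4, for baseline muscle-area Z-score, which is a different quantity.

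**Upper limit.** The two true nulls share no arm. With a large exercise effect, the error is 1 − (1 − 0.05)(1 − 0.05) = 9.75%.

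**Does a smaller Stage 2 level help?** Not enough if Stage 1 stays at 5%:
- Stage 2 at 2.5%: 1 − 0.95 × 0.975 = 7.4%.
- Stage 2 at 5%/3: 1 − 0.95 × (1 − 0.0167) = 6.6%.

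Holm can already spend the whole 5% on NR versus control, so any positive Stage 2 level exceeds 5% once the exercise effect is large.

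**Simulation** (400,000 trials per setting, 16 per arm, pooled variance with 59 df, Stage 2 at two-sided 5%). Under the global null the family-wise error is 4.4%, so the claim holds there. With exercise effective and NR inert:

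| Residual SD | Exercise effect 0.73 Z | 0.93 Z | 1.66 Z |
|---|---|---|---|
| 0.725 (implied) | 6.6% | 8.0% | 9.7% |
| 1.0 | 5.2% | 6.2% | 9.5% |
| 1.4 | 4.1% | 4.9% | 7.6% |

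**Direction.** These are two-sided errors. Counting only false findings of NR benefit, the limit is 1 − 0.975² = 4.94%, and the simulated value at SD 0.725 is about 4.9% at both 0.93 Z and 1.66 Z.

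**Converse case.** If NR works and exercise is inert, the error stays at about 5% or below (4.3% at 0.93 Z).

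**The case against.** **The rule may be fuller than the article shows.** It is called a modification of a cited method, and neither that source nor a separate analysis plan is at hand. If alpha were split, for example Holm at 2.5% in Stage 1 and 2.5% in Stage 2, the limit would be 1 − 0.975² = 4.94% and the claim would be true. This stands as a caveat. But the article describes the rule and claims the property without mentioning a split, and its 95% intervals for each effect point to an unadjusted 5%. Shrinking Stage 2 alone would not be enough.

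**The size depends on an SD that is not stated.** This also stands. If the meta-analytic effect sizes of 0.53 to 0.79 quoted in the article are read as standardised exercise effects, the error is only about 4.2% to 5.6%. A reader might infer that the error is 8% to 10% whenever exercise works. The documents do not support that: it needs an exercise effect of roughly 1.3 SD or more.

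**The consequence is easily overstated.** A reader might also infer that a false claim of NR benefit is twice as likely as stated. It is not; such claims stay at about 5%. Nor does the Stage 2 contrast, taken alone, exceed 5%. The excess comes from Stage 2 and NR versus control together, counted in both directions. The stated primary objective concerns the combination, and that comparison with control is not affected.

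**Conclusion.** The concern holds in this form: the rule as written does not keep the two-sided family-wise error below 5% in every configuration of true and false nulls, contrary to the statements in Statistical considerations and in Sample size and power. That it fails follows from the structure of the rule and needs no assumption about the SD or the exact Stage 2 level, provided Stage 1 Holm is run at 5%. The size does depend on them. At the article's powered effects of 0.93 to 1.66 Z, with Stage 2 at 5%, it is 8.0% to 9.7% at the implied SD of 0.725, 6.2% to 9.5% at SD 1.0, and 4.9% to 7.6% at SD 1.4, with a ceiling of 9.75%. The defect is in a stated guarantee for the primary analysis, and a change of wording with restated power can correct it.

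**What to change.** Put all four contrasts in one family: a single Holm procedure at 5% over the three active-versus-control contrasts and exercise + NR versus exercise. In simulation its family-wise error is at most 5%. State the level for each step and restate the power.

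Cost at SD 0.725, with no change to sample size or conduct:
- Stage 2 power at 0.73 Z falls from 80% to about 71% if NR alone does nothing, or about 77% if NR alone adds 0.73 Z.
- 80% power is reached at about 0.81 Z when the exercise effect is about 0.93 Z. A weaker exercise effect needs a larger difference: at 0.81 Z the power is 77.5% with an exercise effect of 0.5 Z, and 76% with 0.3 Z.
- Power for exercise versus control at 0.93 Z, with NR inert, falls from 90% to about 87%.

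A valid alternative is to test exercise + NR versus control first at 5% and, if it is rejected, apply Holm to the other three. Stage 2 power is similar in these settings, but both single-intervention claims become conditional on the combination result, and power for exercise versus control is about 85%.

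A fixed sequence that places exercise + NR versus exercise ahead of exercise versus control is not advisable. It makes the exercise claim depend on an NR effect: with NR inert and exercise at 0.93 Z, the chance of declaring exercise effective falls from 90% to about 3%.

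If the present rule is kept, delete the below-5% claim in both sections, or state that it holds under the global null and not when exercise is effective and NR is not. If the full rule does split alpha between the stages, the article should say so.
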